## 3.5 Participant Timeline

A detailed schedule of enrollment, randomization, intervention and follow-up is provided in Figure 2. The study involves a 6-week intervention period accompanied with a 20-week follow-up period. Participants will be assessed at baseline, at the end of the intervention period, and at 12, 16, and 20 weeks post-randomization.

## 3.6 Allocation and Blinding

The randomization sequence was generated by an independent statistician using a computerized random number generator (R version 3.6.0). The sequence was designed to ensure a 1:1 allocation ratio between the EA group and the sham EA group. The allocation sequence was concealed using sequentially, numbered, opaque, sealed envelopes. After baseline assessments, a research assistant (uninvolved in recruitment, intervention delivery, or outcome evaluation) opens the next sequentially numbered envelope in the presence of the participant to reveal group assignment. Participants, outcome assessors, and data analysts were blinded to the intervention allocation. The acupuncturists were aware of the group assignment due to the nature of the intervention. Unblinding was permitted only in emergencies (e.g. severe adverse events requiring knowledge of intervention for clinical management).

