## **2.Introduction**

### *2.1 Background and Rationale*

Radical prostatectomy (RP) is a primary treatment for localized prostate cancer (PCa), offering high cancer-specific survival (CSS) at 10-year follow-up, but is associated with early post-prostatectomy urinary incontinence (UI) in 25-86% patients. UI severely impacts patients' quality of life, and existing therapies like pelvic muscle training (PFMT) and artificial urinary sphincters (AUS) exhibit limited efficacy or invasiveness.

Electroacupuncture (EA) combines neuromodulation and Traditional Chinese Medicine (TCM) theory, demonstrating promise in female stress UI but lacking evidence in males. A rigorous evaluation of EA's efficacy and safety in men, using a standardized sham-controlled design, is critical to inform clinical practice. A sham acupuncture protocol was selected to isolate EA's specific effects from nonspecific factors (e.g., placebo, patient-provider interaction). Flat-tip needles applied at sham acupoints mimic EA's tactile sensation without active stimulation, ensuring blinding validity. This approach aligns with recommendations from the Standards for Reporting Interventions in Clinical Trials of Acupuncture (STRICTA) guidelines.

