### *2.3 Trial Design*

This study is a prospective, single-center, randomized, single-blinded, sham-controlled clinical trial designed to evaluate EA's efficacy and safety in men with post-RP UI. Participants are randomized (1:1) to receive either EA or sham EA for 6 weeks, with follow-up extending to 20 weeks post-randomization. Blinding is maintained for participants and outcome assessors, while acupuncturists are unblinded to ensure protocol adherence. The trial adheres to Consolidated Standards of Reporting Trials (CONSORT) guidelines to ensure methodological rigor and transparency.

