## 3.4 Outcomes

### 1) Primary Outcome

UC (define as the use of 0 to 1 pad per day) rate after the 6-week treatment period.

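### Section 3.6 contradicts itself: the envelope is opened with the participant present to reveal the group, yet participants are declared blinded

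*Protocol*

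**What the plan says.** Protocol section 3.6 (Allocation and Blinding) describes sequentially numbered, opaque, sealed envelopes. After the baseline assessments, a research assistant who has no part in recruitment, treatment or outcome evaluation "opens the next sequentially numbered envelope in the presence of the participant to reveal group assignment".

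The very next sentence reads "Participants, outcome assessors, and data analysts were blinded to the intervention allocation". The section goes on to name the acupuncturists as aware of the assignment and states "Unblinding was permitted only in emergencies".

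Section 2.3 (Trial Design) makes the same commitment: "Blinding is maintained for participants and outcome assessors, while acupuncturists are unblinded to ensure protocol adherence".

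Section 2.1 gives the reason for the sham: "A sham acupuncture protocol was selected to isolate EA's specific effects from nonspecific factors (e.g., placebo, patient-provider interaction"). The flat-tip needles are said to "mimic EA's tactile sensation without active stimulation, ensuring blinding validity".

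The primary outcome in section 3.4 is "UC (define as the use of 0 to 1 pad per day) rate after the 6-week treatment period". The section does not say who counts or records the pads.

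**The concern.** The allocation sentence puts the participant in the room and gives revealing the group as the purpose of opening the envelope. Read literally, this routine step discloses EA or sham to a man whom the following sentence calls blinded.

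At stake is the one feature that lets the trial attribute a difference to EA. A man who knows his arm may change how readily he changes a pad, how hard he works at pelvic floor training, how he answers the EPIC-CP questions, or whether he attends all 18 sessions. The number of pads used depends on his behaviour, whoever writes it down, so a blinded outcome assessor cannot remove the effect. The sham would then no longer separate specific from nonspecific effects, and a difference at 6 weeks could be produced by expectation alone.

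**Working it through.** **Step 1. The passages side by side.**

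| Place | What it commits to |
|---|---|
| 3.6, allocation sentence | Envelope opened with the participant present, in order to reveal the group |
| 3.6, next sentence | Participants, assessors and analysts blinded |
| 3.6, last sentence | Unblinding in emergencies only |
| 2.3 | Participants and assessors blinded; acupuncturists not |
| 2.1 | Sham chosen to isolate specific effects, with valid blinding |

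The first row is compatible with the others only if the participant cannot read or hear the content. That would need a coded card, a shielded reading, or a handover to the acupuncturist alone, and the protocol describes none of these. Nor does it say how the acupuncturist, who must know the arm, learns it from an assistant with no part in delivering treatment. The only disclosure it describes is the one in front of the participant.

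**Step 2. The plan's own sample size.** Section 3.8 gives 20% against 48%, two-sided 0.05, 80% power, 10% dropout, and 110 in total (55 per group). Fisher's exact test by enumeration has power 0.789 at 49 per arm and 0.801 at 50. So 50 per arm suffices, and 50 × 1.1 = 55 per arm, or 110. The figure reproduces, and nothing in this point changes it.

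**Step 3. Illustration of size.**

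Inputs from the protocol:
- 55 per arm (3.8; the data analysis plan in 3.8 includes all randomized participants)
- chi-square test, two-sided 0.05 (3.8)
- base continence rate 20% (3.8)

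Input that is assumed and not in the protocol: EA has no specific effect, and awareness of the arm raises the EA rate by δ = 5, 10 or 15 percentage points.

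With n per arm, a continent men on sham and b on EA:

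- p̄ = (a + b)/(2n)
- X² = ((b − a)/n)² / [p̄(1 − p̄)(2/n)]
- P(significant) = Σ Bin(a; n, 0.20) × Bin(b; n, 0.20 + δ), summed over all (a, b) with X² > 3.84

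| δ (points) | EA rate | P(significant), 55 per arm | 50 per arm |
|---|---|---|---|
| 0 | 20% | 0.051 | 0.052 |
| 5 | 25% | 0.097 | 0.093 |
| 10 | 30% | 0.227 | 0.212 |
| 15 | 35% | 0.423 | 0.393 |

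The 50-per-arm column shows the effect of roughly 10% loss. Nearly all of these rejections favour EA: 0.092, 0.226 and 0.423 at 55 per arm for the three shifts.

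**The case against.** The strongest reply is that the protocol never says to whom the group is revealed. The assistant opens the envelope and the participant is merely present. Every other statement points to a blinded participant: two sections say so, only the acupuncturists are named as aware, and unblinding is for emergencies. On this reading the sentence is loosely worded and the practice may have been sound. That stands as far as it goes. A reader might infer that blinding was in fact broken, and the document does not support that inference. The reply does not remove the defect, because the sentence states revealing as its purpose and no safeguard is written down.

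A reader might also infer that the primary outcome is self-reported. Section 3.4 does not say who records pads, and section 3.7 mentions only standardized case report forms. The point does not need the stronger claim: pad use depends on the participant's behaviour in any case. It is also fair to say that the weighed 24-hour leakage, a secondary outcome, is less open to reporting bias.

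Finally, the shifts of 5 to 15 points have no source in the protocol, and the 20% rate is for pelvic floor training alone at 3 months after surgery, not for a sham arm. The figures therefore show what awareness could do to the test, and are no evidence that it did.

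**Conclusion.** The concern holds as an internal contradiction in section 3.6, and between section 3.6 and section 2.3. Followed as written, the allocation step can disclose the arm to the participant. That would undercut the stated reason for the sham and expose the primary outcome. The wording is plainly inconsistent; whether any participant was actually unblinded cannot be settled from this document.

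The size is conditional. With no specific effect, 20% continent in each arm and 55 per arm, assumed awareness effects of 5, 10 and 15 points raise the chance of a significant result from about 5% to about 10%, 23% and 42%. The point must be fixed because it touches the trial's main protection against bias and the correction is nearly free.

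**What to change.** In section 3.6, delete the words that place the participant at the opening of the envelope and give revealing the group as its purpose. State instead that, once baseline assessment is complete, the research assistant opens the envelope out of sight and hearing of both the participant and the outcome assessor, and passes the assignment only to the treating acupuncturist.

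For participants already randomized, record whether the assignment was disclosed and report the numbers by arm. Keep the intention-to-treat analysis of section 3.8 as primary, and do not add an analysis that excludes those who were told. If the step was followed literally, it could remove everyone. If disclosure was partial, it would select on an event after randomization. If disclosure proves to have been routine, the trial should not be described as participant-blinded, and sections 2.1, 2.3 and 3.6 should be amended to match.

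The cost is one sentence, a short retraining of the research assistant and one item on the case report form. Sample size, visits and staffing are unchanged.

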### *3.7 Data Collection and Management*

Data collection will be conducted using standardized case report forms (CRFs). Baseline data include demographic information (age, body mass index [BMI]), medical history (history of hypertension, history of diabetes), unhealthy habits (smoking history, alcohol consumption), oncological features (preoperative PSA, biopsy International Society for Urological Pathology [ISUP] grade group, clinical T stage, Eastern Cooperative Oncology Group [ECOG] status, involvement of pelvic lymph node dissection [PLND], and nerve-sparing status), and initial UC status (number of pads used per day, 24-h pad weight, Expanded Prostate Cancer Index Composite for Clinical Practice [EPIC-CP] UI score). Outcome data will be collected after the 6-week intervention period, and at 12, 16, and 20 weeks post-randomization.

Data management is overseen by an independent DSMB composed of experienced clinical research coordinators and statisticians. The DSMB will ensure the accuracy, completeness, and confidentiality of all study data by conducting monthly comprehensive data checks to identify systematic errors or problems in data entry. Manual checks will be performed to identify more complex and less common errors. Any discrepancies or missing data will be flagged and resolved through communication with the study sites. Only authorized personnel will have access to the data and all data will be anonymized to protect participant confidentiality. Any requests for data access will be reviewed and approved by the DSMB.

### *3.8 Statistical Analysis*

#### *1) Sample Size Calculation*

Based on preliminary data from our institution, the UC rate was 20% for those who performed PFMT alone 3 months postoperatively, 48% for those who underwent 6-week EA treatment. Assuming a two-tailed significant level of 0.05 and 80% power, a total of 110 participants (55 per group) will be required. This calculation accounts for a 10% dropout rate.

#### *2) Data Analysis Plan*

All analyses will be performed using the intention-to-treat (ITT) principle, including all randomized participants. Continuous variables are summarized using means with standard deviations (SD) or medians with interquartile ranges (IQR), as appropriate. Categorical variables are described using frequencies and percentages. For variables, Student t-tests or Mann-Whitney U tests are applied, depending on the data distribution. Chi-square tests are used for categorical variables, and Kruskal-Wallis tests are used for ordinal variables. Statistical analyses are conducted using SPSS software, version 21.0 or higher (IBM, USA) and R software (version 3.6.0 or higher).

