### *3.2 Eligibility Criteria*

#### 1) Inclusion Criteria

- (a) Localized prostate cancer (stage: cT1-cT2, N0, M0);
- (b) 4-6 weeks after robot-assisted RP (RARP);
- (c) Mean 24-h pad number  $\geq 2$ ;
- (d) Prostate-specific antigen (PSA) test below cured level 1 month after surgery;
- (e) Eastern Cooperative Oncology Group (ECOG) performance status of 0-1

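### The primary continence rate gets an unadjusted chi-square test although baseline pad use is collected and not stratified on: valid, but a small and nearly free gain in power and in protection against chance imbalance is passed up

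*Protocol*

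**What the plan says.** Protocol section 3.8, Data Analysis Plan, assigns tests by type of variable. For categorical data it says "Chi-square tests are used for categorical variables". It names no regression model, covariate or stratified test, and it does not mention the primary outcome separately.

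The primary outcome in section 3.4 is "UC (define as the use of 0 to 1 pad per day) rate after the 6-week treatment period", which is binary. Of the tests listed, only the chi-square test fits it.

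Three other places bear on this:

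- Section 3.2 sets entry on the same scale: "Mean 24-h pad number" of at least 2, with no upper limit.
- Section 3.7 lists among the baseline data "initial UC status (number of pads used per day, 24-h pad weight", together with a symptom score.
- Section 3.6 describes the randomization only by its ratio: "The sequence was designed to ensure a 1:1 allocation ratio between the EA group and the sham EA group". No stratification factor is named.

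**The concern.** Baseline pad use is the outcome's own scale measured before treatment. A man who enters at 2 pads has to lose one pad to count as a success; a man who enters at 6 has to lose five. It would be surprising if this did not predict the outcome.

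Neither the described design nor the stated test makes use of it. The three change-type secondary outcomes in section 3.4 are each defined against baseline; the primary outcome is not.

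Two things are at stake. Some power is left unused although the data are on the case report form. And with 55 men per arm, the arms can differ in baseline pad use by chance. If they do, the unadjusted result is open to challenge, and an adjustment added after the fact will look post hoc.

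**Working it through.** **1. The plan's own size.** The rates come from section 3.8: "the UC rate was 20% for those who performed PFMT alone 3 months postoperatively, 48% for those who underwent 6-week EA treatment". The same section sets a two-sided 5% level, a power target of 80%, an allowance of 10% for dropout, and a size of 110 men, 55 in each arm.

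- Pooled two-proportion formula, mean rate (0.20 + 0.48)/2 = 0.34: n = [1.960 × √(2 × 0.34 × 0.66) + 0.842 × √(0.20 × 0.80 + 0.48 × 0.52)]² / 0.28² = (1.313 + 0.539)² / 0.0784 = 43.7, so 44 per arm. After dropout, 44/0.9 gives 49 per arm, 98 in total.
- With continuity correction: 51 per arm. Then 51 × 1.1 = 56.1 (about 112 in total), or 51/0.9 = 56.7, so 57 per arm (114 in total).

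Neither gives exactly 110. The continuity-corrected figure comes closest. Both are unadjusted calculations, so the sample size and the stated test agree with each other.

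**2. Power of the stated test.** With 49 evaluable per arm (110 less 10%): Φ[(0.28 × √49 − 1.313)/0.64] = Φ(1.01) = 84.4%. With 50 per arm: Φ(1.04) = 85.1%. The trial is not underpowered on its own assumptions.

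**3. How often the arms differ at baseline.** Under simple 1:1 allocation the standardized mean difference has standard deviation √(2/n).

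- 50 per arm: √(2/50) = 0.20; the chance of a difference of at least 0.3 SD is 2 × [1 − Φ(1.5)] = 13%.
- 55 per arm: √(2/55) = 0.191; the chance is 2 × [1 − Φ(1.57)] = 12%.

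Half of these favour EA and half go against it.

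**4. What adjustment buys.** The protocol gives no figure for how strongly baseline pads predict continence, so this part rests on assumption: baseline pads distributed as 2 + Poisson(1.5), and an odds ratio of continence of 0.7, 0.6 or 0.5 per extra pad. Simulations used 50 per arm and a logistic model with treatment and baseline pads only. The power column comes from 6,000 trials per scenario and the null columns from 40,000.

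| Odds ratio per pad | Power, 20% v 48%: unadjusted → adjusted | One-sided null rejection, imbalance ≥ 0.3 SD favouring EA: unadjusted / adjusted | Same, imbalance against EA: unadjusted |
|---|---|---|---|
| 0.7 | 85.4% → 86.5% | 4.2% / 1.9% | 1.3% |
| 0.6 | 84.9% → 86.8% | 6.3% / 2.8% | 0.5% |
| 0.5 | 84.9% → 87.9% | 7.6% / 3.0% | 0.6% |

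The null columns use 25% in both arms; the nominal one-sided rate is 2.5%. Over all simulated trials the unadjusted one-sided rate was 2.4-2.6%. At 20% v 44% with an odds ratio of 0.5, power rose from 74.7% to 78.3%. The overall gain is thus about 1 to 4 points.

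When the imbalance goes against EA and the effect is real (20% v 48%), unadjusted power falls to about 66-79%, below the 80% target. Adjusted power stays at about 85-90%.

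**5. Cross-check with a different covariate model.** 49 per arm, a standardized normal covariate, 4,000 trials per scenario (simulation error about 0.6 point), by odds ratio per SD:

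| Odds ratio per SD | Unadjusted | Adjusted |
|---|---|---|
| 1.0 | 85.5% | 86.0% |
| 1.5 | 84.4% | 86.0% |
| 2 | 84.0% | 88.0% |
| 3 | 84.2% | 90.8% |
| 4 | 83.6% | 92.7% |

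The SD of a Poisson(1.5) variable is √1.5 = 1.22, so 0.7 to 0.5 per pad corresponds to 1/0.7^1.22 = 1.5 up to 1/0.5^1.22 = 2.3 per SD. In that range this table agrees with step 4. Two-sided type I error with both arms at 34% was 4.6-5.5% unadjusted and 5.0-5.7% adjusted.

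**6. How large a model the data carry.** Expected events at 50 per arm: 50 × 0.20 + 50 × 0.48 = 34. Treatment plus baseline pads gives 34/2 = 17 events per term; one further covariate gives 34/3 = 11; treatment plus four covariates gives 34/5 = 7.

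**The case against.** The strongest reply is that nothing here is wrong. An unadjusted chi-square test on a randomized binary outcome is valid, the sample size was computed for that kind of comparison, and power exceeds the target. All of that stands, and it caps the severity.

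A second reply is that choice of covariates and the form of the effect estimate commonly sit in a statistical analysis plan, which was not available for this review, and that section 3.8 is only a generic list. This stands in part. The lack of a stated confidence interval is ordinary analysis-plan content and is not raised as a fault. But section 3.8 does state a test for categorical data, and for this outcome a better one is available from data already collected. That is a comment on a stated choice, not on a gap.

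A reader might infer from the 4-8% conditional rejection rate that the trial has an inflated false-positive rate. The documents do not support that. The figure applies only to the 6-7% of trials in which a sizeable imbalance favours EA. In the mirror-image trials the rate is about 1%, and over all randomizations it is nominal.

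A reader might also infer that every listed baseline factor should be adjusted for. With about 34 expected events, and with pads and pad weight both measuring leakage, a four-covariate model is not supported by the calculations here. The protocol gives no figure for the prognostic value of age or nerve-sparing status.

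**Conclusion.** The point holds as a minor improvement to the primary analysis. The stated test is valid, with type I error of about 5% and power of about 84-85% on the plan's rates. Adjusting for baseline pads per day would add about 1 to 4 points of power under assumed odds ratios of 0.7 to 0.5 per pad. The gain is close to nothing if pad use hardly predicts continence, and up to about 9 points if it predicts it very strongly (odds ratio 4 per SD).

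In the roughly 13% of trials with an imbalance of at least 0.3 SD, adjustment holds the one-sided null rejection rate at about 2-3%, where the unadjusted test gives about 4-8% in one direction and about 1% in the other. It also protects power when the imbalance goes against EA. These sizes rest on the assumed distribution and prognostic strength of baseline pads, neither of which the protocol gives.

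**What to change.** In section 3.8, name the primary analysis and fix it before unblinding: a logistic model for UC at 6 weeks with treatment and baseline pads per day, and at most one further covariate. Report it as a standardized marginal risk difference with a 95% confidence interval. Keep the chi-square test as a sensitivity analysis.

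The cost is a few lines of text. No new data, visits or participants are needed. If a separate statistical analysis plan already specifies such a model, section 3.8 should be aligned with it.

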## **4. Ethics and Dissemination**

### *4.1 Ethical approval*

This clinical trial was approved by the Review Board of Nanjing Drum Tower Hospital (2021-083-02) and registered on ClinicalTrials.gov (NCT04972669). The study adheres to the principles of the Declaration of Helsinki and Good Clinical Practice guidelines. All participants should provide written informed consent prior to enrollment in the study.

### *4.2 Protocol Amendments*

Any modifications to the protocol will be documented and submitted to the ethics committee for approval. The trial participants, trial registries and relevant parties will be promptly informed of any significant protocol amendments.

### *4.3 Consent*

Eligible participants receive detailed oral and written explanations of the trial's purpose, procedures, risks and benefits. Signed informed consent forms are obtained by trained research coordinators before enrollment. Participants who are unable to provide consent due to cognitive impairment or other reasons are excluded to ensure voluntary participation. Participants may withdraw consent at any time without affecting their clinical care.

### *4.4 Dissemination Policy*

The results of the trial will be disseminated through peer-reviewed publications, conference presentations, and other relevant scientific forums. The authors will adhere to the guidelines for reporting clinical trials, including the CONSORT and Standard Protocol Items: Recommendations for Interventional Trials (SPIRIT) statement to ensure transparent and accurate reporting of the study findings. The data collected for the present study, including deidentified participant data will be made available to others. These data can be made available following communication with [name] ([name]\[contact]). Before these data are shared (with professional colleagues or other investigators), the request will be

reviewed by [name]. All proposals must be approved by [name], with a signed data access agreement.

